### Study intervention

Patients will be randomized to: 1) an intervention group who will receive a high-protein diet (1.3–1.4 g/kg/day) with low GI; and 2) a control group that will receive a conventional diet that provides approximately 0.8–1.0 g/kg of protein intake. All the patients will be followed for 12 months with nine clinic appointments made by a research dietitian. The evaluations will include nutritional assessment (anthropometrics, body composition, and resting metabolic rate) and laboratory tests.

### Randomization

The randomization will be performed through a simple sequential randomization plan generated online (using the randomization.com website [32]) by another researcher ([name]).

### Blinding

In this clinical trial blinding of patients and dietitians is not possible because of evident differences between the intervention and control group.

### Data collection and timeline

Follow-up evaluation and data collection will be undertaken over 2 years and 6 months at the Clinical Research Center of the Hospital de Clínicas de Porto Alegre, Brazil, by trial personnel. All research tests will be assessed on the same day as protocol laboratory tests.

### Adherence and acceptability

In order to assess diet compliance and safety issues, all participants will collect 24-h urine samples to measure albumin, protein, creatinine, and urea excretion every 3 months. During the first semester, the subjects will have a monthly nutritional visit and, during the second semester, patients will be seen at month 9 and month 12 after randomization.

### Study protocol

Kidney transplant recipients who meet the inclusion criteria and are eligible will be invited to participate in this study 2 months after the transplant surgery. Patients will be randomized to the intervention group or the control group. The intervention group will receive a high-protein (1.3–1.4 g/kg/day) and low GI diet (preference for foods with a glycemic index ≤ 55%, with a daily glycemic load of ≤ 80 g), and the control group will receive a conventional diet (0.8–1.0 g/kg/day of protein). The protein requirement will be re-evaluated 6 months after the baseline. For patients that have lost or gained more than 5% of body weight, the diet will be recalculated. The intervention and control groups will receive energy-matched diets.

Demographic and clinical data will be assessed at the first visit. Nutritional assessment will consist of: a) anthropometric measurements (body weight, height, calculated body mass index (BMI; kg/m^2^), and waist circumference measured midway between the lowest rib margin and the iliac crest, with flexible no-stretch fiberglass tape) performed at each of the nine visits; b) body fat mass (%) measured by bioelectrical impedance analyzer (In Body 230, GE Health Care) assessed every 3 months; and c) resting metabolic rate evaluated by indirect calorimetry (Meta Check 7100, Metabolic Rate Analysis System, KOOR) at baseline and 6 months. All the nutritional measurements will be performed with the patient fasting, wearing light clothing, without contact with metals, and without shoes.

Biochemical assessment will include serum and urine creatinine (assessed monthly), fasting glycemia, cholesterol, high-density lipoprotein (HDL) cholesterol, triglycerides, glycated hemoglobin, and uric acid (assessed every 3 months), high-sensitivity C-reactive protein (at baseline and 6 months), and 24-h urine test for albumin, protein, creatinine, and urea excretion (every 3 months).

The diet prescription will be calculated using nutritional software (Nutribase 2007 Clinical Manager software version 7.14). GI will be estimated as proposed by the Food and Agriculture Organization (FAO) [33] using the international table–United States Department of Agriculture (USDA) table [34], with glucose as the standard food [35] and considering a daily glycemic load of ≤ 80 g. This will be considered as 1.3–1.4 g/kg/day of protein. Energy intake will be assessed by a 24-h recall over nine visits by the research dietitian. Diet composition also will be analyzed using the nutritional table with the software (Nutribase 2007 Clinical Manager software version 7.14) at each visit.

Two months after transplantation, patients are invited to participate in the study protocol and are randomized to the intervention or control group. The intervention group receives the study diet and the control group receives the conventional diet. Both groups visit the center once a month for the first 6 months. After that, another two visits are scheduled at months 9 and 12. At each visit both groups are submitted to the research anthropometric tests and the 24-h recall diet is completed. Besides the prescription of the intervention diet after randomization, the research dietitian reinforces diet adherence at each visit, but only for the intervention group. The standard diet adherence reinforcements are more sporadic for the control group (three to four visits scheduled per year) with the standard dietitian from the hospital. Thus, the intervention group receives eight diet reinforcements and the control group receives three to four reinforcements during the study protocol.

Food intake and adherence to the prescribed diet will be assessed by 24-h recall. An experienced registered dietitian will implement the recall during a face-to-face interview. To assure accurate answers, a photographic album of food portions and household measures will increase the precision of the amount of food consumed. A total of nine records over 1 year will be available for each included patient. Furthermore, the study protocol also includes the collection of urinary urea excretion and this adds to the calculation for the protein equivalent of total nitrogen appearance (nPNA) as a measure of dietary protein intake adherence.

Satiety levels will be assessed twice through a visual analogue scale (VAS) of appetite [36]. This scale will be answered by each patient at home 2 h after three main meals (breakfast, lunch, and dinner) at baseline and 6 months later.

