## Abstract

**Background:**

Excessive weight gain is commonly observed within the first year after kidney transplantation and is associated with negative outcomes, such as graft loss and cardiovascular events. The purpose of this study is to evaluate the effect of a high protein and low glycemic-index diet on preventing weight gain after kidney transplantation.

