## Background

Weight gain after kidney transplantation is very often observed and it has been reported to be between 10% and 35%, mainly during the first year after transplant [1–4]. Post-transplant overweight and obesity may lead to negative post-transplant outcomes, such as graft loss and cardiovascular events [5, 6]. In addition, weight gain during the first year post-transplantation appears to be a risk factor for the development of new-onset diabetes and metabolic syndrome [7–9]. The main factors implied in the weight gain in this population are the immunosuppressive regimen, the cessation of dietary restrictions associated with dialysis, consequent appetite restoration, and improvements in quality of life [10, 11].

Data on nutritional management to prevent weight gain after transplantation is scarce [12–17]. Moreover, the evidence assessing protein requirements in kidney transplant patients is also limited [15, 18]. High protein intake in the early period post-transplant is recommended to match protein catabolism, but there is no evidence available regarding long-term protein requirements of stable renal-transplanted recipients [18].

A high-protein diet is known to be effective for body weight loss and subsequent weight maintenance in the general population [19–22]. Protein generally exerts a better satiety effect than carbohydrates and lipids [23–25]. During the process of weight loss, a high-protein diet preserves lean body tissue, which is the major determinant of resting and 24-h energy expenditure, which, in turn, prevents a greater reduction in energy expenditure [23] usually observed in individuals undergoing a weight reduction program. Besides, it is well known that a diet with a low glycemic index (GI) is determinant of postprandial metabolic responses to food intake and also may have beneficial effects on body weight and body composition [26–28]. Larsen et al. [29] have shown that a dietary plan with moderately high protein associated with a slightly reduced GI leads to weight loss maintenance in overweight adults who had lost at least 8% of body weight. In this context, we designed a randomized clinical trial in order to evaluate the effect of a high protein and low GI diet in preventing weight gain after kidney transplantation.

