## Methods/design

### Study design and centers

This is a prospective, single-center, open-label, randomized clinical trial that will include an interventional group (high protein and low GI diet) and a control group (usual diet) patients that will undergo kidney transplant at Hospital de Clínicas de Porto Alegre, Brazil. The present protocol was written in accordance with Standard Protocol Items: Recommendations for Interventional Trials (SPIRIT) guideline, completing the SPIRIT checklist, and constructing a flow diagram in order to optimize the quality of reporting [30] (Fig. 1 and Additional file 1).

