Since it is not possible to blind participants and researchers involved in this study, there are possible risks of bias. In order to diminish these risks, we will be evaluating standard measurements of weight and other anthropometric and laboratory tests. Furthermore, to reduce the potential for confounding due to measurement variability, a single investigator will perform all the measurements using the same instruments throughout the study and the same dietitian will perform the nutrition intervention protocol.

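### Adherence reinforcement differs by arm in frequency and provider, so a weight difference can be credited to diet plus reinforcement but not to the diet alone

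*Protocol article*

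**What the plan says.** The Abstract gives the purpose as to "evaluate the effect of a high protein and low glycemic-index diet on preventing weight gain after kidney transplantation", and the Background section ends with the same aim: to "evaluate the effect of a high protein and low GI diet in preventing weight gain after kidney transplantation". Study design and centers describes the arms as "an interventional group (high protein and low GI diet) and a control group (usual diet"), with nothing about counselling intensity. The Study protocol section adds that the two diets are matched for energy.

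The same section then describes delivery. After the initial prescription, "the research dietitian reinforces diet adherence at each visit, but only for the intervention group". For controls, who are seen by the hospital's own dietitian, it says: "The standard diet adherence reinforcements are more sporadic for the control group (three to four visits scheduled per year) with the standard dietitian from the" […]. The protocol gives the count itself: "the intervention group receives eight diet reinforcements and the control group receives three to four reinforcements during the study protocol".

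Measurement contact is a separate matter and is equal by schedule: "At each visit both groups are submitted to the research anthropometric tests and the 24-h recall diet is completed". Study intervention gives every patient nine appointments with a research dietitian.

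The Discussion accepts that lack of blinding carries a risk of bias. Its remedies are standard measurements, one person measuring with the same instruments, and that "the same dietitian will perform the nutrition intervention protocol".

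**The concern.** The question asked is about what patients eat. The arms as delivered also differ in how often patients are encouraged to keep to their prescription and in who encourages them. Reinforcement could affect weight by itself, because it acts on adherence to the whole prescription, including its energy content. If the intervention arm gains less weight, the trial cannot tell whether composition, reinforcement or both were responsible. A positive result could then be reported as evidence for high-protein, low-glycemic-index eating after kidney transplantation, a statement that the comparison does not support.

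**Working it through.** **1. Size of the imbalance.** Nine visits less the baseline visit leave 9 − 1 = 8 follow-up visits, which agrees with the eight reinforcements stated. Against three to four in controls, the ratio is 8/4 = 2.0 to 8/3 = 2.7. The provider also differs: research dietitian in one arm, hospital dietitian in the other.

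**2. What the comparison estimates.** Let δ be the effect of diet composition and ρ the effect of the additional reinforcement and different provider, including any interaction with the diet. The difference between arms estimates δ + ρ. The stated aim is δ.

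**3. Whether anything in the plan separates δ from ρ.**

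- Randomisation does not: the difference arises after allocation and is part of each arm as delivered.
- Covariate adjustment does not: by design the counts do not overlap (8 against 3–4) and the provider changes with the arm.
- Matching prescribed energy does not: reinforcement can change how far the prescribed energy is followed.
- The 24-h recalls and urinary urea (nPNA) do not: they describe intake, not why intake or weight changed.
- The bias paragraph in the Discussion does not: its remedies concern measurement and consistent delivery of the intervention.

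**4. The plan's own sample size.** Inputs from Sample size: difference 5, SD 8.8, α 0.05 (two-sided assumed), power 80%.

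n per arm = 2 × (1.960 + 0.842)² × 8.8² / 5² ≈ 48.6, rounded up to 49, so 98 in total. The stated figure reproduces. Power at 49 per arm is 80.3% by the normal approximation and 79.5% by the noncentral t. The point under review does not alter this calculation.

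**5. Illustration on that scale.** The documents give no value for ρ. Assume δ = 0 and ρ = 1, 2 or 3 percentage points. The standard error is 8.8 × √(2/n), which is 1.78 at n = 49 and 1.61 at n = 60. The chance of a significant two-sided t test (noncentral t, noncentrality ρ/SE) is:

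| Assumed ρ | 49 per arm | 60 per arm |
|---|---|---|
| 0 | 5.0% | 5.0% |
| 1 | 8.6% | 9.5% |
| 2 | 20.0% | 23.5% |
| 3 | 38.6% | 45.7% |

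The estimate would be shifted by the whole of ρ, against a target difference of 5.

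**The case against.** A usual-care comparator is a recognised pragmatic choice, and the protocol states the imbalance openly. Randomisation still gives a valid estimate of the package against usual care. All of this stands. A reader might infer that a weight difference would say nothing about the diet, or that the trial is uninformative. The documents do not support that: the diet may well contribute, and only attribution to it alone is lost.

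A reader might also infer that control patients simply see a dietitian less often. The text does not show this. Research visits and recalls are the same in both arms, and controls have their hospital dietitian visits as well. Whether intervention patients keep such hospital visits is not stated. The documented difference is in reinforcement and its provider, not in total contact. Nor is the reinforcement described as weight-control counselling; it concerns adherence to the assigned diet.

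It is also tempting to call the Discussion's remark about one dietitian wrong. It refers to the intervention protocol and is true as written. It makes no claim of equal reinforcement across arms. The gap is that the paragraph leaves the imbalance out.

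Finally, the error rates in the table rest wholly on an assumed ρ, and they use a t test on mean weight change, whereas the stated primary outcome is weight maintenance or gain under 5%. They show that bias is possible, not how large it is.

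None of this answers the central point: the aim is worded as a diet effect, and the design delivers diet plus extra reinforcement.

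**Conclusion.** The concern holds as a point about attribution. Reinforcement is confounded with diet by design, at eight against three to four and with different providers, and nothing planned can separate the two. A difference in weight may be credited to the high-protein, low-glycemic-index diet together with more frequent reinforcement by the research dietitian. It may not be credited to diet composition alone, which is how the aim and arm definitions would have it read. This conclusion rests on the protocol's own description of delivery and needs no assumption about effect size. The size of any resulting bias is unknown; the 9% to 46% range depends on an assumed effect of 1 to 3 points.

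**What to change.** Restate the aim, the primary comparison and the planned interpretation as *high-protein, low-glycemic-index diet plus intensified dietitian reinforcement versus conventional diet with usual reinforcement*, and make no claim about diet composition alone. Add the imbalance in frequency and provider to the Discussion's paragraph on risk of bias, which now covers only lack of blinding and measurement variability. This is a change of wording with no effect on the 98 evaluable or 120 enrolled patients. The cost is a narrower claim.

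Equalising reinforcement for patients not yet randomised is an option for the sponsor to weigh, not a required change. Trial status reports that sixty patients have started, so about 120 − 60 = 60 remain. Both arms already attend the same visits, which makes it practical. It would, however, need an amendment during recruitment and would create two control conditions. Comparisons within each period would have about 30 per arm, with roughly 58% power for the full 5-point difference at SD 8.8 (two-sided, before dropout).

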### Primary outcome

The primary outcome will be weight maintenance and weight gain under 5% of body weight.

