**Methods:**

We designed a prospective, single-center, open-label, randomized controlled study to compare the efficacy of a high protein (1.3–1.4 g/kg/day) and low-glycemic index diet versus a conventional diet (0.8–1.0 g/kg/day of protein) on preventing weight gain after kidney transplantation. A total of 120 eligible patients 2 months after transplantation will be recruited. Patients with an estimated glomerular filtration rate through the modification of diet of renal disease (MDRD) formula < 30 mL/min/1.73 m^2^ or urinary albumin excretion > 300 mg/24 h will be excluded. Patients’ diets will be allocated through simple sequential randomization. Patients will be followed-up for 12 months with nine clinic appointments with a dietitian and the evaluations will include nutritional assessment (anthropometrics, body composition, and resting metabolic rate) and laboratory tests. The primary outcome is weight maintenance or body weight gain under 5% after 12 months. Secondary outcomes include body composition, resting metabolic rate, satiety sensation, kidney function, and other metabolic parameters.

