### Sample size

Sample size calculations were carried out in WINPEPI 11.20 (Brixton Health, Israel) based on data from Souza et al. [31]. To find a difference of 5% in body weight between groups 1 year after the transplant, considering a standard deviation of 8.8%, a significance level of α ≤ 0.05 and a statistical power of 80%, the minimum sample size will be 98 patients. Because of possible dropouts, we will include 120 patients (60 randomized to each group).

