## Discussion

To the best of our knowledge, this is the first randomized clinical trial that will evaluate the impact of a high protein and low GI diet on weight maintenance or weight gain lower than 5% of body weight after kidney transplantation. Furthermore, this study will evaluate other relevant parameters related to metabolic outcomes since we hypothesized that this dietetic intervention may be able to improve body composition, resting metabolic rate, satiety, inflammation, and lipid and glycemic profiles.

Importantly, there is still concern related to a high protein intake and kidney damage based on some previous studies that showed an association between a high protein intake and worsening of renal function [37–40]. However, data on the impact of protein intake on long-term outcome in kidney transplant recipients are scarce [40–43]. Bernardi et al. evaluated a low-protein, low-lipid, and low-sodium diet in a 12-year follow-up study and showed a protective effect for the kidney with this diet [40], but the interpretation of the results are limited and controversial. Van Den Berg et al. [41] studied the association between protein intake and blood pressure, proteinuria, and creatinine clearance in a cross-sectional study with 625 renal transplant recipients, and no deleterious effects of the diet were identified. Interestingly, in a cohort of 940 kidney transplant recipients, a higher protein intake was associated with protection against mortality and graft failure [42]. These results were confirmed in a more recent cohort of 604 kidney transplant recipients with 7 years of follow-up [43]. Said et al. have shown that a high protein intake was associated with improvements in muscle mass and with reduced risk of mortality and graft failure [43], suggesting that a relatively high protein intake may be beneficial to kidney transplant recipients.

Other studies evaluating the impact of dietary interventions in kidney transplant recipients show conflicting results, mainly limited by the study design [12–14]. Thus, due to lack of high-quality evidence data on this issue, there are no guidelines or recommendations for a specific nutritional intervention to manage weight gain and obesity after kidney transplantation [44–46].

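### The primary outcome is worded inconsistently and does not say how weight loss counts; its time point does not match the sample size, and the placing of loss can change the result

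*Protocol article*

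**What the plan says.** The protocol article describes the primary outcome in three places.

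- Primary outcome section: "The primary outcome will be weight maintenance and weight gain under 5% of body weight". It gives no reference weight, no time point and no rule for weight loss.
- Abstract, Methods: "The primary outcome is weight maintenance or body weight gain under 5% after 12 months". The connective is now *or*, and a duration appears without an origin.
- Discussion: "weight maintenance or weight gain lower than 5% of body weight after kidney transplantation". Again *or*, with transplantation as the only anchor in time.

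The Sample size section uses a continuous target and a different clock: "To find a difference of 5% in body weight between groups 1 year after the transplant", with an SD of 8.8%, 5% significance, 80% power and a minimum of 98 patients, raised to 120 (60 per group). The Study protocol section places invitation and randomisation two months after surgery. The Adherence and acceptability section counts follow-up from there: "patients will be seen at month 9 and month 12 after randomization".

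The only symmetric 5% band in the article is a rule for the diet, not an outcome: "For patients that have lost or gained more than 5% of body weight, the diet will be recalculated".

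**The concern.** Maintenance is never defined, and no section says whether a patient who loses weight has met the outcome. Loss is foreseeable, because the abstract's Discussion paragraph says that this kind of diet may produce it. If the diet lowers weight by the planned amount, more intervention than control patients will lose over 5%. Calling them successes or failures therefore moves the comparison in opposite directions.

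The clocks also disagree. Randomisation at month 2 after transplant plus 12 months is month 14 after transplant. One year after transplant is month 10 after randomisation, which lies between the month 9 and month 12 visits. The sample size thus names a time at which no visit is scheduled.

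The trial is open-label and 60 patients had started when the article was written, so the definition is best settled before the arms are compared.

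**Working it through.** **Inputs from the Sample size section:** difference 5 points, SD 8.8%, alpha 0.05, power 80%, 60 per group.

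**Assumptions, not in the article:** percent weight change is normal with SD 8.8 in both arms; the intervention mean is 5 points below control; the control mean runs from +2.5% to +15%. The Background cites gains of 10% to 35%, mainly in the first year after transplant. That is only a loose guide here, because follow-up starts at month 2.

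**Step 1: the plan's own figure.** For two means, n per arm = 2 × (1.960 + 0.842)² × 8.8² / 5² = 48.6, rounded up to 49, or 98 in total. This matches the stated 98 with a two-sided test. Power for this comparison is 80% at 49 per arm and 88% at 60 per arm. The figure belongs to a continuous mean difference.

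**Step 2: two readings of success.** With control or intervention mean μ:

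- A, any change below +5% (all loss counts as success): Φ((5 − μ)/8.8)
- B, within ±5% (loss above 5% fails): Φ((5 − μ)/8.8) − Φ((−5 − μ)/8.8)

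Example, control +10% and intervention +5%:

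- A: Φ(−0.568) = 28.5% v Φ(0) = 50.0%, difference 21.5 points.
- B: 28.5 − 4.4 = 24.1% v 50.0 − 12.8 = 37.2%, difference 13.1 points.

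Power for a responder comparison is Φ((d − 1.960 × SE₀)/SE₁), where d is the difference in proportions, SE₀ is pooled and SE₁ unpooled.

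| Control mean | A: control v intervention | A: difference | B: control v intervention | B: difference | A − B | Power of A, 60/arm |
|---|---|---|---|---|---|---|
| +2.5% | 61.2 v 80.3% | 19.1 | 41.5 v 41.5% | 0.0 | 19.1 | 64% |
| +5% | 50.0 v 71.5% | 21.5 | 37.2 v 43.0% | 5.8 | 15.7 | 68% |
| +7.5% | 38.8 v 61.2% | 22.4 | 31.0 v 41.5% | 10.4 | 11.9 | 69% |
| +10% | 28.5 v 50.0% | 21.5 | 24.1 v 37.2% | 13.1 | 8.4 | 68% |
| +12.5% | 19.7 v 38.8% | 19.1 | 17.4 v 31.0% | 13.7 | 5.4 | 64% |
| +15% | 12.8 v 28.5% | 15.7 | 11.6 v 24.1% | 12.4 | 3.3 | 57% |

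(Differences are in percentage points, from unrounded values.)

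The column A − B equals the between-arm difference in the share losing more than 5%: for example 28.5 − 12.8 = 15.7 points at control +5%, and 12.8 − 4.4 = 8.4 at control +10%.

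**Step 3: power of the responder comparison.** Reading A, the more favourable of the two, has 57% to 69% power at 60 per arm over this range. At 49 per arm it has 48% to 60%. It would need 156 to 208 patients in total for 80% power.

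**Step 4: what cannot be sized.** The article gives no weight trajectory, so the effect of the two-month shift, or of taking weight at transplant rather than at randomisation as the reference, cannot be calculated.

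**The case against.** The best defence is that the intended meaning is plain. Maintenance and a gain under 5% cannot sensibly be joint conditions, so *and* reads as a list of acceptable results, as the abstract and Discussion confirm. The stated aim is throughout to prevent weight gain, which is one-sided and makes a patient who loses weight a success. This largely stands: under that reading the change from *and* to *or* alters no patient's classification.

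A reader might infer from the diet-recalculation rule that a loss above 5% is an outcome failure. The article does not say so. That sentence concerns the prescription, and it shows only that a ±5% meaning of maintenance is conceivable.

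A reader might also infer that the definition will be chosen after the data are seen. Nothing shows this, and a fuller protocol or analysis plan, not shown here, may settle reference weight and handling of loss. What such a document would not remove is the conflict in print between the three wordings and between the two clocks. The time point itself is largely recoverable as month 12 after randomisation; only the Sample size section clearly departs from it.

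Finally, the size depends on a control mean that the article does not give. At gains of 10% or more the two readings lie within about 8 points of each other.

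**Conclusion.** The inconsistency is real and should be fixed. The substantive part is the unplaced weight loss. Under the plan's 5-point difference and SD of 8.8%, counting any change below +5% as success gives a difference of about 16 to 22 points, and counting only changes within ±5% gives 0 to about 14. This assumes normality, equal SDs and a control mean between +2.5% and +15%.

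It would be too strong to say that the wording decides the trial. That holds mainly at low control gain, where one reading shows a clear benefit and the other little or none; at +15% the readings are 15.7 v 12.4 points. Nor is the sample-size arithmetic wrong: 98 reproduces exactly, but for a mean difference rather than for the responder category that the outcome wording suggests.

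**What to change.** Use one definition in the abstract, the Primary outcome section and the Discussion:

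- Percent change = 100 × (weight at month 12 after randomisation − weight at randomisation) / weight at randomisation.
- Responder = change below +5%, with any loss counted as a responder, in line with the aim of preventing gain. Losses above 5% are tabulated separately by arm.

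Restate the sample-size time point as month 12 after randomisation, about month 14 after transplant. State that 80% power with 98 patients applies to the continuous mean difference, and that the responder comparison has at most about 69% power at 60 per arm (about 57% to 69% over the control means assumed here).

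Make the change before any between-arm comparison. It needs amendment wording and no new measurement, since weight is already scheduled at every visit. The real cost is a less favourable stated power for the responder outcome.
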